### **Data Analysis**

Data will be entered using an Oracle-based data management system. Data analysis will be directed by [name], with full participation of the research team to interpret and publish findings. Primary analyses will compare relative risks (Aim 1) or means (Aims 2-5) between groups defined by pre-treatment infection status or treatment group, according to the specific aims.

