## 1. Study Protocol

### Aims Of The Project

**Aim 1:** To test whether community-based periodic treatment of children 6-23 months old with mebendazole will decrease rates of severe anemia and protein-energy malnutrition by at least 20%.

**Aim 2:** To determine whether young children infected with intestinal nematode infections exhibit a more pro-inflammatory response to nematode antigens (i.e. characteristic of T Helper 1 [Th1] cells) than age-matched uninfected children.

**Aim 3:** To test whether mebendazole treatment of infected children reverses this pro-inflammatory response.

**Aim 4:** To measure intestinal blood loss related to relatively light hookworm infection in young children, and whether intestinal blood loss is reduced after treatment with mebendazole.

**Aim 5:** To elucidate metabolic mechanisms that could explain the link between a pro-inflammatory cytokine response and anemia and protein-energy malnutrition. Specifically, we aim:

A) To determine whether newly infected children show defects in iron metabolism compared to age-matched uninfected children, in a manner consistent with mechanisms of the “anemia of chronic disease” (i.e. decreased iron absorption, decreased iron incorporation into erythrocytes, suppressed erythropoiesis, and/or shortened red cell life span);

B) To determine whether newly infected children catabolize protein at greater rates than age-matched uninfected children;

C) To determine whether newly infected children are more anorexic than age-matched uninfected children.

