To answer **Aim 4**, a subsample of 300 children will be constructed of hookworm-negative (n=100), light hookworm infections (1-999 epg, n=100) and moderate hookworm infections ( $\geq 1000$  epg, n=100). These classifications are lower than typically used in school children, and were chosen for children 6-24 month who have lighter infection intensities but whose total body iron store is limited or absent. Therefore small quantities of GI blood loss could have significantly alter their iron balance. Intestinal blood loss will be measured in this subsample at just prior to treatment, and 1 and 12 months post-treatment. This HemoQuant subsample will be drawn from the Immunology Subsample, so that immunologic data will also be available.

To answer **Aims 5A and 5B**, a subsample of 20 newly-infected and 20 uninfected (total n=40) children will be selected from the Immunology Subsample. This number, although small for an epidemiologic study, is large for a metabolic study involving stable isotopes. To our knowledge it is the largest sample size ever involved in a similar protocol. However, many factors may affect the metabolism of these children and it is essential to limit the heterogeneity within this sample to reduce variance unrelated to the factors of interest (i.e. helminth infection status and cytokine response). Thus, we will impose inclusion criteria based on age (12-23 months old), wasting malnutrition (weight-for-height Z scores  $\geq -1$ ), recent illness (no significant morbidity in the prior 2

weeks, and malaria infection (<1000 parasites/mL). Because these children will be drawn from the age-matched triplets defined for the Immunology study, the 20 children in the newly-infected group and the uninfected groups will be further matched on age within the 1-year-old age category.

**Specific Aim 5C** will be addressed using maternal reports of poor appetite, a method that is valid and very simple to implement. Therefore anorexia will be assessed in the full sample of 2500 children just prior to treatment and at 3, 6 and 12 months post-treatment.

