### Justification Of Sample Size

Our starting point for the sample size calculation was the Immunology Subsample. The proposed starting sample size of about 750 children, after 15% attrition, provides 220 children per infection status group, randomly allocated into 2 treatment groups. Thus to compare treatment effects within infection groups, we plan to have about 110 children. Based on the ongoing work of Drs. [name], [name], and [name] in Nanjing China, where they are using the whole blood assay to assess cytokine responses to *Schistosoma mansoni*, 100 per group is a minimum number to detect important differences.

To generate this number of age-matched triplets for the Immunology Subsample, about 2500 children will need to be screened for infection. This will in fact be more than enough to address Aim 1. However, we propose to retain the entire group of 2500 children for several reasons. First, we want to retain the representative community-based sample to address Aim 1. The Immunology Subsample will be specifically constructed such that it is no longer representative of the community of young children. We want to make inference about the effects that would be observed if mebendazole treatment were provided to all young children in this environment, since screening for infection status would be impossible to implement in a public health program. Second, it has been our experience in Pemba that once community meetings have been held to inform and motivate participation in a research study, it is difficult to randomly select only some of the children into the actual study. Because participation in the study will confer some benefits to the study subjects and their communities, families resent being excluded from community-based studies. Third, the costs of implementing the Full Sample protocol are relatively small.

The sample size for the HemoQuant Subsample, 100 per infection intensity group, was based on our previous HemoQuant study of hookworm-related blood loss in Pemba school children. In that study we detected significant differences amongst infection intensity groups with 50 children per group, however, the spectrum of infection intensities in school children was much greater. Because infection intensities will be light in these young children, we have doubled our previous sample size to detect smaller blood losses.

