### **Assessment Methods For Full Sample**

Helminth infection will be assessed by fecal egg counts determined by quantitative formalin ether concentration technique. Presence and intensity of GI nematode infections will be assessed by the Formol ether method on a weighed amount of mixed feces ( $\approx 1$  g). The eggs present in the whole sediment will be counted in McMaster chambers except if very high numbers of a particular species is present, in which case a known proportion of the graduated slide will be counted.

Anemia will be assessed by hemoglobin concentration using the HemoCue method. When capillary blood samples are assessed (full sample protocol), the third drop of blood will be used. Severe anemia will be defined as hemoglobin  $< 7$  g/dL.

Malaria parasite density will be determined by counting parasites against leukocytes in a thick blood film, according to standard methods.

Anorexia will be assessed by maternal recall using established techniques.

PEM will be assessed by weight, length, and arm circumference-for-age following standard protocols.

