#### **Additional Assessment Methods For HemoQuant Subsample**

Intestinal bleeding will be assessed by the HemoQuant assay. This assay measures the quantity of heme excreted per gram of feces. In subjects who consume little red meat intake (like young Pemban children), this is an accurate measure of intestinal blood loss.

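### Aim 4 compares mean blood loss across three bands of a measured egg count; a pre-specified regression on the count should be added, for a power gain of roughly 0 to 40 points depending on the shape of the relation

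*Protocol*

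**What the plan says.** Aim 4 (Aims Of The Project) is "To measure intestinal blood loss related to relatively light hookworm infection in young children", and also asks whether mebendazole reduces that loss.

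Under Experimental Design and Methods, "a subsample of 300 children will be constructed of hookworm-negative (n=100), light hookworm infections (1-999 epg, n=100) and moderate hookworm infections"; the last band starts at 1000 epg.

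The exposure is a count: "Helminth infection will be assessed by fecal egg counts determined by quantitative formalin ether concentration technique" (Assessment Methods For Full Sample). The outcome is also quantitative. Of HemoQuant the Protocol says "This assay measures the quantity of heme excreted per gram of feces".

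The sample size rests on an earlier study in school children: "In that study we detected significant differences amongst infection intensity groups with 50 children per group". For the present trial, "Because infection intensities will be light in these young children, we have doubled our previous sample size to detect smaller blood losses" (Justification Of Sample Size).

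The Data Analysis section then fixes the primary method: "Primary analyses will compare relative risks (Aim 1) or means (Aims 2-5) between groups defined by pre-treatment infection status or treatment group". It speaks of infection status. The three intensity bands as comparison groups come from the design and sample-size sections. No analysis of Aim 4 with the count as a continuous term is stated.

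**The concern.** A child with 1 epg and a child with 999 epg receive the same exposure value, and so do all children from 1000 epg upwards. The Protocol expects light infections and small losses, the setting in which exposure information is least affordable. Its only stated response is to double the group size. Band means also depend on which counts happen to fall within each band, and they do not give an expected loss at a given egg count. What is at stake is power to show that blood loss rises with infection intensity, and the ability to describe that relation.

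**Working it through.** **1. The Protocol's own figure.** It gives no alpha, power, SD or difference for this subsample, so only 2 × 50 = 100 per group can be reproduced. Assuming two-sided 0.05 and 80% power, the detectable pairwise difference in SD units is (1.960 + 0.842) × √(2/n):

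- n = 50: 2.802 × 0.200 = 0.56
- n = 100: 2.802 × 0.141 = 0.40

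Doubling multiplies the detectable difference by 1/√2 = 0.71, a 29% reduction.

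**2. Band means against the count, main simulations.** From the Protocol: 100 children per band and the band limits. Assumed: log10 epg normal with mean 2.5 and SD 0.7, drawn within bands; residual SD 0.6 on log heme; two-sided 0.05. The comparison is the three-group F test against a joint 2-df test of a square-root count term plus an infected-versus-negative indicator.

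| Assumed relation of log heme to eggs | Three-group test | Joint regression test | Gain (points) |
|---|---|---|---|
| Proportional to count | 57% | 93% | 36 |
| Proportional, with counting error | 59% | 88% | 29 |
| Square root of count | 65% | 81% | 16 |
| Log count | 44% | 44% | 0 |
| Log count, 40 children in the top band | 33% | 34% | 1 |

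A further run under a log relation gave 59% for the joint test and 60% for the group test.

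**3. A second set with other assumptions.** Counts are log-normal: median 200 truncated to 1-999, and median 1800-2000 truncated at 1000 and above. Effect size is set by a correlation r of 0.10 to 0.25, and a single count term is used. Gains over the three-group test were:

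- proportional relation, raw-count term: 21 to 38 points (for example 72% v 34% at r = 0.15); 26 to 53 with a heavier tail; 16 with counting error of log-SD 0.7
- square-root relation, raw-count term: 3 to 12 points
- log relation, log-count term: 2 to 13 points

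**4. Where the gain comes from.** Under the proportional relation of step 2, among negative and light children only, the t test had 6% power, square-root regression 7% and log regression 6%. Regression therefore does not help that contrast; the gain lies in the higher counts. With 40 rather than 100 children in the top band, a single square-root term fell from 96% to 69%, and the group test from 59% to 35%.

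**5. Cost of a wrong scale.** Under a log relation, a single square-root term had 42% v 45%, 72% v 79%, 52% v 59% and, with 40 in the top band, 38% v 42% for the group test: a loss of 3 to 7 points. A single raw-count term did much worse (37% v 63% at r = 0.15, a loss of 26). The joint test in step 2 stayed within about 1 point.

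**The case against.** The strongest reply is that banding is a sound sampling design, that three ordered means already show a gradient, and that one sentence limited to primary analyses does not bar a regression in an SAP that is not shown. Under a log relation, a simple trend test over the same three bands almost matches log-count regression (73% v 76% at r = 0.15). All of this stands. It limits the size of the point but does not remove it: the Protocol does name a primary method, and that method ignores the count within bands.

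Four stronger readings are tempting and not supported.

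- A reader might infer that Aim 4 asks for a dose-response. It does not; it names neither a slope nor a loss per egg. Intensity enters through the bands.
- A reader might take a gain of 30 to 40 points as the expected one. The documents give nothing from which to derive it. It needs loss close to proportional to eggs and skewed counts.
- A reader might think regression rescues the comparison of light with negative children. Step 4 shows it does not. An estimate at light intensity from the regression is borrowed from heavier infections through the fitted curve. Nor is that comparison without power under every shape: in the second set it had about 5-6% under the proportional relation, 6-21% under the square root and 20-81% under the log, over the r values tried.
- A reader might conclude that the group means should be demoted to description. For the question as written, light versus negative is the direct estimate, and it should stay.

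The treatment half of Aim 4 compares arms and is not weakened by banding in the same way.

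**Conclusion.** The point holds as a worthwhile improvement; the plan states nothing false or contradictory here. The stated primary comparison for Aim 4 discards within-band intensity information that the trial already collects, while the Protocol expects small losses. Adding a joint regression test gains roughly 0 to 40 points of power: most if loss is proportional to eggs, about 16 under a square-root relation, and about none under a log relation. The 53-point figure belongs to a single raw-count term under a proportional relation with a heavy tail, which is neither the recommended model nor a safe one. All these figures rest on assumed egg distributions, residual SD, slopes and alpha, because the Protocol gives none for Aim 4. The benefit concerns the overall relation of blood loss to intensity, not the light-versus-negative contrast.

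**What to change.** Keep the three strata for sampling. Keep the group means, including light versus negative, as the direct answer for light infection. Beside them, pre-specify a regression of log fecal heme on a transformed egg count, adjusted for age: for example a square-root term plus an infected-versus-negative indicator, tested jointly, with a log-count version as a check on shape. Report predicted loss with confidence intervals at stated counts, such as 100, 500 and 1000 epg, and say that the values at light intensity depend on the fitted curve. Leave the treatment-arm comparison as it is.

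The cost is a few lines of analysis text; no child, visit or sample is added. The real downside is that the scale must be chosen before the data are seen. A single square-root term loses about 3 to 7 points if the relation is logarithmic, while the joint test stays about level with the group test.

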### **Collaboration**

The collaboration between The Johns Hopkins University and the Ministry of Health of Zanzibar has been ongoing since 1994. The focus has been epidemiologic research on the relations between parasitic infections, anemia and malnutrition. The London School of Hygiene and Tropical Medicine (LSHTM, [name], [name]) is currently collaborating with the PHL to investigate whether Zanzibari school children are acquiring resistance to mebendazole after more than a decade of mass treatment with that drug. They are also collaborating with Nanjing Medical University to study cytokine and antibody responses and resistance to infection with *Schistosoma japonicum* in humans. This proposal unites the nutrition and epidemiology expertise of JHU with infectious disease immunology expertise of the Immunology Unit at LSHTM and the applied health research experience and needs of the Pemba PHL. Each contribution is essential. In June 2000, Ministry of Health of Zanzibar opened the Pemba PHL to serve as a semi-autonomous research body of the MOH. The proposal is designed to equip the PHL with training and technology related to epidemiology, parasitology, and metabolism.

### **Training And Technology Transfer**

Three forms of training are integrated into the research plan. The first is MSc training at an African Institution for one Zanzibari scientist, for whom parts of this research will comprise his/her thesis research. Second, 2 senior local scientists ([name], [name], and the MSc trainee) will participate in the 3-week Summer Epidemiology Course offered by JHU in project years 1, 2, and 3. This will allow each one to take a total of 6 short intensive courses (2 per year) in epidemiology and biostatistics. Third, 2-person teams from the Immunology and Parasitology Departments of the PHL will receive practical training on assessment techniques both at the PHL and in LSHTM laboratories. The foci of the training will be the whole blood assay under the direction of Drs. [name] and [name], and measurement of acute phase proteins under the direction of [name]. Practical training in each of these areas will include two parts: First, a 3-week trip to the US or UK laboratory to learn the method, followed by a visit of the UK or US scientist to the PHL to supervise the establishment of the method in the PHL. In addition to training of personnel, this proposal will provide the Pemba PHL with key laboratory equipment that will serve not only this research plan, but a wide variety of research endeavors in years to come. This equipment is detailed on page 27. The research plan is designed so that all laboratory work will be conducted at the Pemba PHL, with the exception of the analysis of stable isotopes by mass spectrometry which requires very specialized and expensive instruments.

